# Functional outcome of total knee replacement: a study protocol for a prospective, double-blinded, parallel-group randomized, clinical controlled trial of novel, personalized and conventional implants

**DOI:** 10.1186/s12891-019-2830-7

**Published:** 2019-10-12

**Keywords:** Knee osteoarthritis, Arthroplasty, Total knee replacement, Novel designs, Functional outcome, Prospective studies, Clinical protocols

## Abstract

**Background:**

The development of total knee replacement (TKR) implant designs aims to improve outcome regarding pain, function, joint stiffness, instability, patellar problems, and ultimately wear of the implant. Recently, two major orthopaedic implant manufacturers launched a new generation of TKR implants which, according to the manufacturers, provide improved functional outcome. However, the benefits of these new TKR designs claimed by the manufacturers in terms of improved functional outcome still lack scientific documentation. The present randomized controlled trial has been designed to compare three fixed bearing, cemented cruciate-retaining (CR) designs; one of the new personalized TKR design with two conventional TKR designs with the main emphasis being on functional outcome.

**Methods:**

The present study is a prospective, double-blinded, randomized, single-center intervention trial. A total of 240 patients will be recruited to participate in a parallel-group study at Coxa Hospital for Joint Replacement, Tampere, Finland. We will compare the short-term functional outcome of TKR performed with a novel personalized TKR design (Persona CR, Zimmer, Warsaw, IN, USA) against TKRs performed with two conventional designs (PFC CR, DePuy, Warsaw, IN, USA and Nexgen CR, Zimmer, Warsaw, IN, USA). In total, 80 patients will be randomized in each of the three study arms. The primary outcome in this study is the Oxford Knee Score (OKS), which is a validated patient-reported outcome measure (PROM). Secondary outcome measures include the Forgotten Joint Score, the 15D, the UCLA activity score, and the VAS pain scale. The results will be analyzed after 2-year follow-up.

**Discussion:**

This paper presents a prospective, randomized, single-center trial study protocol. It provides details of patient randomization, PROMs, follow-up, methods of analysis of the material, and publication plan. An important aspect that will be considered in the study will be the economic effects of the novel designs as they are substantially more expensive, and the benefits of the added costs remain unknown. In addition, it is especially important to carry out evaluative studies in independent centers that are not biased by the interests of the manufacturers.

**Trial registration:**

Retrospectively registered, November, 2017, ClinicalTrials.gov Identifier: NCT03339557.

## Background

Total knee replacement operations are well-documented and effective treatments to decrease pain and improve function in patients with end-stage arthritis of the knee joint [1–3]. Moreover, knee replacements have been shown to be effective both clinically and in terms of cost effectiveness [4, 5]. Demand for joint replacement operations has continuously increased, and future projections suggest that this trend will continue [6], which will pose increasing demands on health care systems.

Although joint replacement surgery is widely considered to be one of the success stories of modern medicine, approximately up to 20% of patients with a knee replacement are to some extent dissatisfied with the outcome following their joint replacement operation [7–9].

### Evaluation of treatment

Measuring the outcome of total knee replacement surgery is challenging. Earlier, implant survival, i.e., the absence of revision surgery, was the most referenced measure of success. With contemporary implants and surgical techniques, the survival of most knee implants has been shown to be excellent even in long-term follow-up, as reported by many national joint registries [10–14]. Moreover, most implant designs have cumulative revision rates below 1% per annum, a target level set by the National Institute of Healthcare and Clinical Excellence (NICE) [15]. Recently, however, more emphasis has been put on patient satisfaction. Patient reported outcome measures scores (PROMs) have been introduced and used instead of traditional surgeon-based clinical assessments [16, 17]. One of the most widely used PROMs is the Oxford knee score (OKS), which is also included in the National Joint Registry for England and Wales data as an outcome measure [11, 18]. Other commonly used PROMS include the Visual Analogue Scale (VAS), the health-related quality of life (15D), and the UCLA activity score [19, 20]. At present, however, there is no single score or method for the assessment of all outcome aspects with widespread agreement, and newer and more sensitive scores, such as the “Forgotten joint score” (FJS), have been introduced to better capture the differences in function after TKR in more active patients [21–23].

### Previous studies

In addition to the patient related factors, surgical technique as well as the knee replacement design used influence the outcome [24] . Based on large registry data, it has been postulated that the effect of surgical factors, including implant type, are modest when compared with patient related factors [25].

The significance of implant design on knee function has been widely studied [26–29], as there is broad variability in implant concepts and specific designs. Numerous studies, however, have been unable to detect any differences in function between the most commonly used cruciate retaining (CR) or substituting, posterior stabilised (PS) concepts [26, 28]. Using the OKS as an outcome measure, one registry-based study showed that the performance of one implant type was statistically significantly better than all of the other most used contemporary implant designs [24]. However, the differences between the groups were not even close to the recently described minimally clinically important difference [30]. On the other hand, one small study showed that refining a well performing knee design did not influence the functional outcome [31] . In contrast to this finding, a new design was reported to improve the OKS score of TKR patients in a cross-sectional setting [32]. However, due to obvious limitations in study settings, these results must be interpreted with caution.

The effect of implant design on the outcome of knee replacement surgery is clearly being emphasized by the implant manufacturing industry. New, personalized and hopefully improved implant designs are the target of intensive research and development projects. A more anatomically accurate implant, finer sizing increments and full continuum of bearing constraints is redefining personalization. Recently, two major orthopaedic implant manufacturers both launched a new generation total knee replacement implant on to the market. Both of these implant systems are based on the legacy of their predecessors, which have been among the most implanted and best-documented designs globally. The clearly stated aim of these new systems is to improve functional outcome with less pain, joint stiffness, instability, patellar problems, and ultimately wear of the implant. However, the benefits claimed for these new or redesigned models in terms of improved outcome still lack scientific documentation. Cost is also an important aspect as the novel designs are substantially more expensive, and therefore the benefits of the added costs remain unknown. Furthermore, it is especially important to carry out evaluative studies in independent centers that are not biased by the interests of implant manufacturers.

### Study objective

The aim of this randomized controlled trial is to compare one novel, personalized TKR implant design (Persona CR, Zimmer, Warsaw, IN, USA) against two conventional TKR design (PFC CR,DePuy, Warsaw, IN, USA and NexGen CR, Zimmer, Warsaw, IN, USA) in terms of functional outcome and cost-effectiveness.

## Methods

The study design is a prospective, double-blinded randomized controlled, single-center trial adhering to Standard Protocol Items: Recommendation for Interventional Trials (SPIRIT) guidelines. The study will be carried out at Coxa Hospital for Joint Replacement (Tampere, Finland), a university-affiliated publicly-funded orthopaedic hospital specializing in joint replacement surgery. Currently, more than 4000 joint replacements are performed annually (representing approximately 20% of all hip and knee replacements performed annually in Finland), of which 2000 are primary knee replacement operations. Coxa Hospital is responsible for joint replacement surgery in Pirkanmaa Hospital District with a catchment area population of ca. 550,000 inhabitants, and it also serves as a tertiary referral hospital for one-fifth of Finland.

### Primary and secondary outcome measures

The primary outcome is the Finnish language version of the OKS (33) measured both preoperatively**,** and postoperatively at 2–3, 12, and 24 months. The OKS is a validated and reliable PROM. The questionnaire comprises 12 items regarding pain and activities of daily living (ADL) specifically related to the knee. Each item is scored on a five-level Likert scale 0 (worst disability) to 4 (no disability). The total score can range from 0 to 48, with 48 being the best possible score. The minimal clinically important difference (MCID) depends on the purpose of the comparison: it has recently been defined as 5 points, when different patient cohorts are compared against each other [18, 30, 33, 34]. Thus, in this study, a > 5-point difference in median OKS at 24 months postoperatively between any of the three cohorts studied (Persona CR, PFC CR, and NexGen CR) will be defined as a clinically significant difference in functional outcome.

The secondary measured outcomes both preoperatively, and after surgery at 2–3, 12, and 24 months are the FJS, the 15D, the UCLA activity score, and the VAS pain scale.

The FJS is an assessment tool designed especially for well-performing patients and describes the patients’ ability to forget the artificial joint in everyday life. The questionnaire comprises 12 items regarding and integrating pain, stiffness, function in ADL, patients’ activity levels, and psychosocial factors. Each item is scored on a five-point Likert response format of 1 (never) and 5 (mostly), and scores are summed and linearly transformed to a 0 to 100 scale. The high scores indicate good outcome, equaling a high degree of forgetting the replaced joint during ADL [17, 22, 35]. The validity and reliability of the FJS has been reported to be good, with a lower ceiling effect than the OKS [36].

The 15D is a generic, comprehensive (15-dimensional) self-administered instrument for measuring health-related quality of life (HRQoL)(19). The questionnaire comprises 15 dimensions with 5 ordinal levels on each dimension. From each dimension, the respondents choose the level that best describes their present health status. A set of population-based preference and utility weighs is used to generate the 15D score on a 0 (being dead) to 1 (full health) scale. Moreover, the 15D scores are generalizable and valid for deriving quality-adjusted life years (QALYs). The generic MCID for the change of 15D scores are ±0.15 [19, 37].

The 10-point University of California Los Angeles (UCLA) activity score has 10 descriptive activity levels ranging from wholly inactive (level 1) to regular participation in impact sports (level 10) [20].

The visual analogue scale (VAS) pain score, comprising a scale from 0 (no pain) to 10 (worst imaginable pain), is used to evaluate pain. In cost-effectiveness analysis, cost of surgery, hospitalization, out-patient visits and physiotherapy visits will be calculated. Cost per quality-adjusted life-years will be analyzed.

To further analyze the differences and complex relationships between pain experience and joint function, a sample of synovial tissue will be analyzed for patient specific factors associated with inflammation and inflammatory pain. These analyses will include immunohistology and measurements of gene expression and polymorphism relating to modulating pain and inflammatory reaction.

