### Sample size

The power analyses will be calculated using both the OKS (primary outcome) and the FJS (secondary outcome). Of these, the FJS is more sensitive in differentiating patients at the upper end of the outcome scores and requires larger patient groups. With the OKS, the estimated sample size is 48 patients per arm. With the FJS in the range of 60 to 80 and a standard deviation of 25 points, the estimated sample size is 64 patients per arm (delta = 13, sd = 25, alpha = 0.05, power = 0.8). Allowing for a 10% drop-out rate and a 10% addition due to skewness in the variable distribution, the required arm size is 80. Therefore, with three comparison arms, the total number of patients recruited into the study will be 240.

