### Statistical methods

Descriptive statistics, including mean and standard deviation, for continuous variables will be used. Differences between groups in continuous skewed main outcome variables will be analyzed using the Mann-Whitney U-test, and t-test when variables are normally distributed. Results will be presented with 95% confidence intervals. Two-way-tables with the chi-square test will be used for dichotomous variables, and multivariate analysis will be conducted with regression analysis. The α-level will be set at 0.05. SPSS Statistics version 23 (IBM Corp., Armonk, NY) will be used for the analysis.

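### The OKS criterion for clinical significance (a median gap of more than 5 points) excludes a gap equal to the 5-point MCID from which it is derived

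*Protocol article*

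**What the plan says.** All the relevant text on the threshold is in the protocol article, Primary and secondary outcome measures.

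- On the MCID, the article says that "it has recently been defined as 5 points, when different patient cohorts are compared against each other".
- The next sentence, introduced as following from this, sets the trial's criterion as "a > 5-point difference in median OKS at 24 months postoperatively between any of the three cohorts studied".
- On the scale: "Each item is scored on a five-level Likert scale 0 (worst disability) to 4 (no disability", with 12 items, and "The total score can range from 0 to 48, with 48 being the best possible score".

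No other section restates the threshold. Sample size gives only a result for the primary outcome, "With the OKS, the estimated sample size is 48 patients per arm", with no OKS difference or SD that would show which boundary was meant.

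**The concern.** A minimal clinically important difference of 5 means that 5 is the smallest difference that matters. A criterion of strictly more than 5 places that value on the unimportant side, although the article presents the criterion as derived from the MCID. On a continuous scale the distinction would be academic. Here the summary is the median of a whole-number score, so a gap of exactly 5 can occur with appreciable probability.

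At stake is the label put on the primary outcome. Trials that observe exactly the stated MCID would be reported as showing no clinically significant difference. For that label the error runs in one direction, towards the first hypothesis, that the three designs give similar OKS results.

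**Working it through.** **1. What the boundary does on this scale.** Twelve items scored in whole points from 0 to 4 give whole-number totals from 0 to 48. An arm median is a whole number when the arm size is odd, and a whole or half number when it is even. A gap of exactly 5.0 is therefore attainable. The next larger gap is 6 if both medians are whole numbers and 5.5 if one falls on a half point. Relative to the MCID: 5.5/5 = 1.10 and 6/5 = 1.20, so the rule in effect asks for 10% to 20% more than the MCID.

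**2. Can the sample size settle which boundary was meant?** The 48 per arm cannot be reproduced, because the article gives neither the OKS difference nor its SD. It can only be solved backwards, assuming two-sided alpha 0.05 and power 0.8 (the values stated for the Forgotten Joint Score, with two-sidedness assumed):

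SD = difference × √(48/2) / (1.960 + 0.842)

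- Difference 5: 5 × 4.899 / 2.802 = 8.74 (8.65 with the t distribution)
- Difference 6: 6 × 4.899 / 2.802 = 10.49

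So 48 per arm is compatible with a target of 5 but does not establish it. An SD of 8.7 is used below as an assumption.

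**3. How often the boundary is hit, one pair of arms.** Simulation with 40,000 replicates per setting: normal scores with SD 8.7, rounded and capped to 0–48, better-arm mean 40, true difference 5. Arm sizes are 80 (planned), 72 (80 × 0.9, after the stated 10% drop-out) and 71 (a neighbouring odd size).

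| n per arm | median gap exactly 5 | labelled under > 5 | labelled under ≥ 5 |
|---|---|---|---|
| 71 | 21–22% | 39–40% | 61% |
| 72 | 13% | 43–44% | 56–57% |
| 80 | 14% | 43% | 57% |

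Ranges show the spread between repeat runs. With a true difference of 4 or 6 the two rules differ by 11 to 12 percentage points at n = 72.

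**4. The same check on means.** Under the same model, a mean gap of exactly 5 occurs in about 0.4% of trials at each arm size.

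**5. Sensitivity to the assumed distribution.** With skewed scores (scaled beta on 0–48, mean about 36) and a true gap of 5, the exact-5 share is:

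- SD 8.7: about 16% at n = 71, 9% at n = 72 and 10% at n = 80.
- SD 7 to 10: about 22% to 13% at n = 71, and about 15% to 8% at n = 80.

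The absolute chance of being labelled moves much more. At n = 80 it is about 63–76% under > 5 and 78–84% under ≥ 5.

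**6. Cost when the arms are equal.** The rule covers any of three cohorts, hence three pairs. Under the model in step 3 with no true difference, the chance that at least one pair is labelled is:

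| n per arm | > 5 | ≥ 5 | rise (points) |
|---|---|---|---|
| 71 | 0.8% | 3.9% | 3.1 |
| 72 | 1.0% | 2.6% | 1.6 |
| 80 | 0.6% | 1.9% | 1.3 |

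Repeat runs move these figures by about 0.2 points.

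**The case against.** The strongest reply is that little depends on this. The criterion is a label. Statistical methods separately specifies tests ("The α-level will be set at 0.05") and 95% confidence intervals, so a gap of 5 would still be reported with its interval. Requiring a difference to exceed the MCID can also be defended as a stricter convention, and it makes a favourable claim for the novel implant harder too. The first part stands and limits the severity. The second would stand if the article said it was choosing a stricter rule, but it presents the criterion as following from the MCID.

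A reader might infer that the defect applies equally to means. The wording conflict does, but the practical effect does not: 0.4% against 13% to 22%. This matters because Statistical methods also describes means and a t-test for normally distributed variables.

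A reader might also infer that the article declares a 5-point gap unimportant, or that the trial will conclude similarity from this rule alone. It says neither. The exclusion of 5 follows only from the definition, and the tests and intervals are reported alongside.

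The objection that the size rests on assumptions also stands. The SD is back-solved, and the shares are conditional on a true gap of exactly 5. A skewed distribution with the same SD gives about 9% to 16%.

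Lastly, the change is late. Recruitment ran from September 2015 to August 2018 and the article appeared in October 2019, so the earliest patients had already passed 24 months. Relaxing a primary-outcome criterion at that stage needs a date and a reason.

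**Conclusion.** The point holds, as a minor inconsistency. The stated MCID is 5, the criterion derived from it is more than 5, and nothing in the article reconciles them. Because the criterion is set on medians of whole-number scores, a gap equal to the MCID is classed as not clinically significant, and one pair of arms would land on that value in about 13% to 22% of trials. That range assumes a true gap of 5, an SD of about 8.7, rounded and capped normal scores, and 71 to 80 patients per arm. The significance test, its alpha level and the planned 80 per arm are unaffected.

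**What to change.** In Primary and secondary outcome measures, replace the strict inequality with *a difference of 5 points or more (≥ 5)*. Use the same boundary wherever the 24-month OKS difference and its confidence interval are interpreted. Record it as a dated clarification, with the reason, made before anyone sees unblinded 24-month results.

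The change needs no further patients or data. Its price is the rise in step 6: with three equal arms, the chance of labelling some pair clinically significant goes from about 1% or less to about 2% to 4%, an increase of 1.3 to 3.1 percentage points.

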Strict inclusion criteria are a possible limitation of our study and may result in selection bias, as a good number of patients had to be excluded. Therefore, even random allocation may end up in heterogeneity of intervention arms. However, the inclusion criteria are set to focus on the most common type of patient, i.e., patients with primary uncomplicated osteoarthritis of the knee. The upper age limit was set to 70 years to also obtain outcome data on the more active younger TKR patients, who tend to end up at the upper end of the outcome scores after TKR surgery. In theory, this approach might help us to better differentiate “good” outcome from an “excellent” outcome, especially if such subtle differences are found between the implant designs that would not become evident in the older, less active patient groups. On the other hand, if a novel knee design cannot provide these younger and generally more active patients with an improved functional outcome, it will certainly not do so in other patient groups either.

Introducing a new TKR implant system is a known risk factor for failure in joint replacement [40]. This poses the danger of a type 2 error in hypothesis 1, as the surgeons are more familiar with the conventional implant systems and the outcome of the novel TKR design may be inferior due to surgeon-related factors. To avoid this pitfall, we arranged a formal training of the novel implant system and allowed each of the participating surgeons to perform approximately 10 surgeries with the novel implant before commencing the random allocation.

The longevity of contemporary TKR designs is excellent, but the functional outcome and patient satisfaction levels still leave room for improvement. Functional outcome is, however, the result of complex interplay, where the implant design is only one factor and patient characteristics and the surgeon performing the implantation play major roles as well. The development of TKR implants is a continuous activity, where the manufacturing industry plays a leading role. The evaluation of novel designs must be carried out according to strict scientific methods to be able to differentiate the influence of the three major factors – the implant, the patient, and the surgical performance – from each other. In addition, it is especially important to carry out these evaluative studies in independent centers, and not to be biased by the interests of implant manufacturers.

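### The 5-point clinical threshold is set on median OKS, which neither planned test targets and no planned interval is tied to, and on a scale capped at 48 its behaviour depends on where the arms lie

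*Protocol article*

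**What the plan says.** All references are to the protocol article.

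- **Threshold.** Primary and secondary outcome measures takes the minimal clinically important difference from cited work: "it has recently been defined as 5 points, when different patient cohorts are compared against each other". It then sets the trial's own yardstick as anything greater than a "5-point difference in median OKS at 24 months postoperatively between any of the three cohorts studied", which "will be defined as a clinically significant difference in functional outcome". The quantity judged is thus the "point difference in median OKS", not a difference in means.
- **Scale.** The same section states: "The total score can range from 0 to 48, with 48 being the best possible score". It also credits the FJS with a lower ceiling effect than the OKS.
- **Analysis.** Statistical methods plans a Mann-Whitney U-test for skewed main outcomes and a t-test for normally distributed ones, at alpha 0.05 with 95% confidence intervals. It does not say which quantity the intervals describe. On summaries it says: "Descriptive statistics, including mean and standard deviation, for continuous variables will be used". It does not mention medians.
- **Expected distribution.** Sample size adds 10% for skewness. The Discussion explains that the age limit brings in younger, more active patients, "who tend to end up at the upper end of the outcome scores after TKR surgery".
- **Use of a null result.** Hypothesis i predicts similar OKS results for all three designs. The Discussion says that if the novel design does not help these patients, "it will certainly not do so in other patient groups either".

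**The concern.** The clinical question is put to one quantity and the statistical question to another. When a score is skewed and bounded, the median gap, the mean gap and the rank-based shift can differ a good deal. A significant test can then sit beside a median gap that fails the yardstick, or a median gap above 5 can come from a much smaller mean gap, and the plan does not say which is the result.

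The cap adds a second problem. As the comparator's median approaches 48, the room for a better arm shrinks below the threshold, while the room for a worse arm does not. Because the primary hypothesis is similarity, a yardstick that cannot register an advantage would favour that hypothesis, and the Discussion would carry the null to patients who were not studied.

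**Working it through.** **1. The plan's own figures.** The plan gives no calculation for the median rule. For the OKS it states 48 per arm without a difference or an SD. Using n = 2·SD²·(1.96 + 0.84)²/δ² with δ = 5, SD = 5·√(48/2)/2.80 ≈ 8.7. So 48 fits a 5-point *mean* difference with SD about 8.7, but that is back-solved, not stated. The arm size of 80 comes from the FJS (δ 13, SD 25) and reproduces as 64/0.8 = 80. The 64 itself does not: the same formula gives 59, or 60 with the t-distribution. It corresponds to a standardised difference of 0.5. The gap is conservative and does not bear on this point.

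**2. Ceiling arithmetic.** Largest possible advantage = 48 − comparator median.

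| Comparator median | Largest advantage | More than 5 possible? |
|---|---|---|
| 40 | 8 | yes |
| 42 | 6 | yes |
| 43 | 5 | no |
| 44 | 4 | no |

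**3. Behaviour of the rule.** Assumptions: 72 per arm (80 × 0.9); scores are 48 × a beta variable, rounded to integers, matched to a chosen mean m and SD. With μ = m/48, v = (SD/48)² and k = μ(1 − μ)/v − 1, the beta parameters are μk and (1 − μ)k. For m = 40 and SD 8.65, μ = 0.833, v = 0.0325 and k = 3.28, so the parameters are 2.73 and 0.55 and the median is 43. Simulation gives:

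| True means | SD | True medians | Median gap >5 | Mean gap >5 |
|---|---|---|---|---|
| 39 vs 36 | 8.65 both | 42 vs 38 | 23% | 8% |
| 40 vs 36 | 8.65 both | 43 vs 38 | 51% | 25% |
| 41 vs 36 | 8.65 both | 45 vs 38 | 81% | 51% |
| 44 vs 40 | 6 (upper), 8.65 | 47 vs 43 | 9% | 21% |

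The second and fourth rows share a mean gap of 4. The cut-off on means moves little between them (25% to 21%), but the median rule falls from 51% to 9%. In the fourth row Mann-Whitney power is about 96%. The rule is met there only when the sampled comparator median happens to fall below 43.

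**4. Where the comparator median may lie.** In the same model the median reaches 43 at a mean of 40 with SD 8.65, or 41 with SD 7. At a mean of 39 (SD 8.65) it is 42, and at 36 it is 38; the rule can be met in both.

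**5. No true difference.** The chance that any two of three observed medians differ by more than 5 is about 2% (median 36–38, SD 8.7), 0.6% (median 40, SD 8) and about 0% (median 43, SD 6).

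**6. Precision under normality.** With SD 8.74, the standard error of the mean difference is 8.74·√(2/72) = 1.46. For the median difference it is 1.46·√(π/2) = 1.83.

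**The case against.** The strongest defence is that the plan has a test and, separately, a yardstick borrowed from the literature, and that how an interval is read against 5 is commonly left to an analysis plan not shown here. That is fair as far as it goes. The text defines clinical significance; it does not say that significance is declared from the observed gap alone, and intervals are promised. But the yardstick is explicitly on medians and the tests are explicitly not. That mismatch is stated, not merely left open.

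Four stronger readings are tempting and do not hold.

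- *A better novel implant cannot be declared.* This is true only if the comparator's median is 43 or more. No expected OKS median is given, and the upper end of the scores is not a number.
- *The rule works against the novel design.* Mid-scale the skew does the opposite: at means 41 vs 36 the median rule is met in 81% of trials, against 51% for means. The handicap appears only near the ceiling.
- *The sample size ignores the 5-point difference.* For the OKS the inputs are unstated, and 48 per arm fits a 5-point difference.
- *At a true gap of 5 the rule succeeds only 43% of the time while the test has 93% power.* This compares a cut-off placed at the true effect with a test of zero. Any measure would meet such a cut-off about half the time, and the drop from 50% to 43% comes from rounding.

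The defence can also say that the FJS was included for its lower ceiling effect and drives the sample size. That helps the trial as a whole, but the FJS is secondary and does not alter the rule for the primary outcome.

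**Conclusion.** The point stands in limited form. The protocol article sets its clinical threshold on a quantity that the planned tests do not target outside symmetry or a pure shift, and ties no interval to it. On a skewed integer score capped at 48, how often the same mean gap meets the rule depends strongly on location: about 51% against 9% for a mean gap of 4 in the two settings shown, where a cut-off on means gives 25% and 21%. These percentages rest on the assumed beta shape, the chosen SDs and 72 per arm.

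The ceiling bound is arithmetic and needs no model, but whether it applies depends on a median that the documents do not give. The acknowledged OKS ceiling effect and the patients recruited make it plausible, not certain. False declarations under no difference are rare (about 2% or less in the settings tried) and are not the weakness. This should be corrected before analysis; it does not invalidate the design.

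**What to change.** - Name one effect measure for the 24-month OKS that matches the test used: the mean difference, adjusted for baseline since baseline OKS is collected, or the Hodges-Lehmann shift if the rank test is kept.
- Report it with its 95% confidence interval and interpret that interval against the 5-point minimal important difference. State whether exactly 5 counts, since the cited value is 5 and the rule asks for more than 5.
- Report medians and the share of patients at or near 48 descriptively, so that readers can see how much room the scale left.
- Remove the Discussion's statement that the design "it will certainly not do so in other patient groups either", and limit a null conclusion to the enrolled population aged 50–70.

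No new data are needed. The cost is more than wording: the headline summary moves from a median gap to another measure after recruitment closed in August 2018. The change should be dated and documented as made before analysis.
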